### *3.3.5 Data collection*

The study teams at SC CTSI and USC Norris will be provided with tracking sheets to collect data on the prospective participants and enrollees. For example, the SC CTSI team will track information on who was contacted via Twitter, when a Twitter user was contacted, their online engagement with the recruitment message, and if they used the contact form on the clinical trial web page to contact the study team. The USC Norris team will use a tracking sheet to track information about the prospective participants that were screened, their response, and whether an enrollee of a USC Norris cancer trial had been contacted through the investigators' program. Please see **Table 3** for an overview of all primary outcome measures and **Appendix 5** for the data dictionary that list all metrics the study team will use to characterize the success of the intervention.

Study data will be collected using the system REDCap (Research Electronic Data Capture) at USC. REDCap is a secure, web-based application designed to support data capture for research studies [40], providing: 1) an intuitive interface for validated data entry; 2) audit trails for tracking data manipulation and export procedures; 3) automated export procedures for seamless data downloads to common statistical packages; and 4) procedures for importing data from external sources. Provision of data to the IRB, NIH, and FDA is facilitated by this database system.

Verbitum transcription of audio recorded interviews will be reviewed for completeness. Transcripts of interviews will be entered and managed using Atlas.ti, a qualitative data management computer program.

### *3.3.6 Data security and confidentiality*

The data will only be viewed by the study team for this project. Identifiers such as name, Twitter user name, age and gender data are collected and stored in a secure, HIPAA-compliant database REDCap at USC for no longer than 1 year and will be deleted after that time. We won't store the IP addresses of respondents. Names of non-eligible individuals will not be maintained. The data for analysis will be de-identified.

To support research transparency and reproducibility, we will share the de-identified research data after publication of the study results. We will share the de-identified data on Figshare (Figshare.com), a repository where users can make all of their research outputs available in a citable, shareable and discoverable manner. We will use a data-sharing agreement that provides for: (1) a commitment to using the data only for research purposes and not to identify any individual participant; and (2) a commitment to securing the data using appropriate computer software.

### *3.3.7 Data analysis*

Feasibility will be assessed by describing the acceptance of and satisfaction with the SM recruitment method among USC Norris study team members and Twitter users in LA County, number of cancer trials eligible to be enrolled in study at the time of this study (current estimate of 84 is based on latest data from USC Norris), number of cancer disease types and studies that can be monitored for on Twitter simultaneously by the SC CTSI study team, time and effort it takes the SC CTSI and USC Norris team members to respond to the

resulting inquiries and decide whether or not to bring the patient in for screening, eligibility rate of prospective participants, demographic and ethnic diversity rate of those who consented/enrolled, social media message click rate, website contact form usage rate, social media message click rate, website contact form usage rate. **Table 3** lists all primary outcomes measures we intend to use.

To facilitate qualitative data analysis, we will develop an initial code list based on the interview guide. The code list will be modified throughout the coding process. Each coded transcript will be discussed line by line until the coding team came (Drs. [name] and [name]) to an agreement about code definitions and how they should be applied. Important themes will be summarized and used to understand satisfaction with SM-based recruitment strategies for cancer-related clinical trials.

Count outcomes will be presented as median and interquartile range, nominal outcomes will be presented as N (%). We will explore patient and study characteristics between the two cohorts to examine where differences might lie by including them as potential covariates in the models. Comparisons of the before- and after time periods will be made using generalized estimating equations for appropriate outcome type (Poisson, means, prevalence) accounting for type of cancer.

The **efficacy** aim will be determined comparing monthly actual vs. projected rate of recruitment for the trial disease groups (i.e., non-small cell lung cancer, colon cancer, breast cancer, prostate cancer, kidney cancer, lymphoma) and compared to historic data by trial disease group using generalized estimating equations, accounting for intra-disease random effects and trends across the 12 months (9 months exposure per trial). Statistical analyses of primary aims will be carried out by [name] [name], an SC CTSI biostatistician. Analyses will be performed in SPSS v24 [41]. As this is a pilot study, p-values are of limited use to determine group differences, so we will focus on observed effect sizes (Cohen's D, Relative Risk).

**Table 3** lists all primary outcomes measures we intend to use. In addition, **Appendix 5 (data dictionary)** provides the full set of metrics we will use to assess the success of the intervention, which includes additional success metrics such as number of contacts solicited, number of contacts who acknowledge the solicitation, number of social media contact/recruitment messages sent, day/time of contact, day/time of response.

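### The impact analysis names two incompatible models for six disease groups, and lists Cohen's d beside relative risk without saying which applies to monthly enrolment counts

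*Protocol*

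**What the plan says.** Section 3.3.7 sets out the efficacy analysis: monthly actual against projected recruitment, plus a comparison with past accrual, in six named disease groups. The stated method is "using generalized estimating equations, accounting for intra-disease random effects"; time trends over a 12-month span are to be allowed for as well. The Analysis plan row of the Synopsis uses the same model wording. For the before/after comparison, section 3.3.7 says that it "will be made using generalized estimating equations for appropriate outcome type (Poisson, means, prevalence) accounting for type of cancer".

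On reporting, it says that "p-values are of limited use to determine group differences, so we will focus on observed effect sizes", and in the same sentence names two measures, Cohen's d and relative risk. On covariates, patient and study characteristics are to be explored "by including them as potential covariates in the models". The software is SPSS v24.

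No confidence level, variance estimator, reference distribution or clustering unit is stated. Estimating the effect size is a study objective (1.3.2) and a primary outcome (Synopsis). Table 4 says that the preliminary data are to support a larger grant proposal.

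**The concern.** **Model.** GEE is a marginal method with a working correlation. Random effects belong to a mixed model. The two give different standard errors and, in general, different estimands, so an analyst cannot tell which one is planned.

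**Clusters.** The robust (sandwich) variance used with GEE relies on many clusters. If disease is the cluster, there are six.

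**Effect size.** For counts, the standard deviation rises with the mean. Cohen's d therefore depends on how busy a disease group is as well as on the relative gain.

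**Covariates.** Characteristics of enrolled patients exist only for people who enrolled, and diversity of enrolled participants is itself a primary outcome (Table 3). Adjusting a recruitment count for them would condition on something the intervention may change.

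The effect size and its precision are what the pilot hands to the larger study. An interval that is too narrow, or a d that mixes base rate with effect, would carry over into that study's planning.

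**Working it through.** The protocol gives no coverage, power or sample-size figure for this model, so there is nothing to reproduce.

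**Base rates.** Appendix 2, interventional therapeutic accruals, 2012–2016 totals divided by 60 months:

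| Disease | Total | Per month |
|---|---|---|
| Lung | 134 | 2.23 |
| Colon | 305 | 5.08 |
| Breast | 461 | 7.68 |
| Prostate | 315 | 5.25 |
| Kidney | 149 | 2.48 |
| Lymphoma | 47 | 0.78 |

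The window from 2016 to 27 June 2017 gives about 2.8, 3.9, 5.4, 4.1, 0.62 and 0.73 in the same order.

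**Coverage, analytic.** With six equal clusters, the uncorrected sandwich in effect divides by 6 instead of 5. A 1.96 limit then covers with probability P(|t₅| < 1.96·√(5/6)) = P(|t₅| < 1.789) = 86.6%.

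**Coverage, simulated.** Poisson GEE on six diseases at the 2012–2016 rates, 9 post-months, robust standard error with 1.96. Assumptions not in the protocol: true rate ratio 1.2; SD of the disease-specific log effect (τ) 0 or 0.3; SD of the disease-by-year log rate (σ) 0 or 0.3; 12 or 60 pre-months. There were 1,500 runs per cell (800 with disease dummies), so the Monte Carlo error is about 1 to 1.4 points.

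| Pre-months | τ | σ | Period only | With trend and stagger | With disease dummies |
|---|---|---|---|---|---|
| 12 | 0 | 0 | 83.3% | 85.1% | 84.8% |
| 12 | 0 | 0.3 | 83.1% | 82.3% | 80.6% |
| 12 | 0.3 | 0 | 81.3% | 83.0% | 79.2% |
| 12 | 0.3 | 0.3 | 81.6% | 81.1% | 82.0% |
| 60 | 0 | 0 | 84.4% | 84.5% | 84.4% |
| 60 | 0 | 0.3 | 79.3% | 80.8% | 81.0% |
| 60 | 0.3 | 0 | 79.5% | 80.3% | 78.4% |
| 60 | 0.3 | 0.3 | 80.1% | 82.3% | 79.4% |

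Runs at 2016 rates lie between 79.3% and 87.1%. A separate simulation (2016 to mid-2017 rates, 18 pre-months, rate ratio 1.3, exchangeable correlation, 2,000 runs) gives 83%, 83% and 79% for τ = 0, 0.2 and 0.4. Overall the range is about 79–87%; the one cell at 78.4% is within Monte Carlo error of 79%.

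**Small-sample correction.** Common intercept and period, 12 + 9 months, 400 runs per cell, independence or exchangeable correlation:

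| Interval | Coverage |
|---|---|
| Robust, 1.96 | 80–86% |
| Robust, t on 5 df | 89–93% |
| Bias-reduced (Mancl–DeRouen), 1.96 | 86–93% |
| Bias-reduced, t on 5 df | 93–96% |

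For contrast, clustering on 84 independent trials gives 95% with the ordinary robust interval.

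**Cohen's d.** For Poisson means m and RR·m, d = (RR − 1)·m / √((m + RR·m)/2). At RR = 1.5 this is 0.5·√m/√1.25 = 0.447·√m.

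- 2012–2016 rates: lymphoma 0.447·√0.78 = 0.40; breast 0.447·√7.68 = 1.24.
- 2016 to mid-2017 rates: kidney 0.447·√0.62 = 0.35; breast 0.447·√5.4 = 1.04.
- At RR = 1.2 and 2012–2016 rates, d runs from 0.17 (lymphoma) to 0.53 (breast).

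The ratio of largest to smallest is √(7.68/0.78) ≈ 3.1 or √(5.4/0.62) ≈ 3.0, whatever the RR.

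**The case against.** **Relative risk is already planned.** The sentence reads "so we will focus on observed effect sizes (Cohen's D, Relative Risk"). A reader might infer that Cohen's d is the sole effect size; it is not. Since the models cover counts, means and prevalence, d may be meant for means only. What stands is that the text does not say so.

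**No interval is promised.** A reader might infer that the protocol commits to intervals covering about 80%. It fixes no level, variance estimator or reference distribution, it plays down p-values because this is a pilot, and a SAP could add a correction. Also, 80% is near the low end of the range. The coverage point is therefore a conditional risk.

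**Six clusters is a reading.** The clustering unit is never named. Accrual targets are set per trial (3.3.3), 84 trials are expected, and Table 3 counts contacts per trial per month. However, section 3.3.7 speaks of intra-disease effects and disease groups, and the accruals in Appendix 2 are by disease only.

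**Covariates are only to be explored.** A reader might infer that the recruitment count will be adjusted for enrolled-patient characteristics. The text speaks of potential covariates across several outcome types, and includes study characteristics. The Synopsis also lists the number of open trials, amendments and status changes as exploratory variables. What stands is that nothing keeps patient characteristics out of the count model.

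The contradiction between GEE and random effects is untouched by any of this.

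**Conclusion.** The point holds as a specification fault with a quantified risk. The model contradiction is on the page, in both section 3.3.7 and the Synopsis. The likely size of the under-coverage, 79–87% for a nominal 95%, rests on three conditions: disease is the cluster, the robust variance is uncorrected, and normal limits are used. It also depends on the assumed rate ratio, heterogeneity and pre-period. The roughly threefold spread in d needs only Poisson counts and the protocol's own accrual figures, and appears with either choice of base rates. It matters only if d is applied to monthly counts, which the text leaves open. The covariate issue is a matter of closing off a permitted misuse.

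**What to change.** Name one log-link count model for monthly enrolment, with period, trend and an offset for open trial-months (the number of open trials is already among the exploratory variables). Then choose one of:

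- **(a)** a Poisson or negative binomial mixed model with a random disease intercept and a random disease period effect, and small-sample degrees of freedom; or
- **(b)** a GEE clustered on disease with a common intercept, bias-reduced standard errors and t on about 5 df, in software that supports it.

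Option (b) should not carry a dummy for each disease. With one dummy per cluster, the matrix that the Mancl–DeRouen correction inverts is singular (smallest eigenvalue 0, against 0.83 with a common intercept). The 93–96% coverage was obtained for the common-intercept model without trend or offset, so the final model should be checked by simulation before it is fixed.

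For counts, report the rate ratio and the extra enrolments per month with intervals. Keep Cohen's d for continuous outcomes. Describe enrolled-patient characteristics by period but leave them out of the count model; study-level characteristics may stay.

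The cost is wording in the protocol or SAP and a little analysis work. The downside is wider intervals and possibly a procedure other than the default SPSS GEE.

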| Analysis plan                                         | 1. Feasibility will be assessed by describing the acceptance of and satisfaction with SM recruitment method among USC Norris study team members and Twitter users in LA County and by describing the proportion of eligible cancer trials to be enrolled in the study, cancer disease types and studies that can be monitored for on Twitter at a time, time and effort it takes the SC CTSI and USC Norris team members to respond to the resulting inquiries and decide whether or not to bring the patient in for screening, eligible participants that can be enrolled, demographic and ethnic diversity of participants, and staffing required to monitor eligible studies.
2. Impact : The efficacy aim will be determined comparing monthly actual vs. projected rate of recruitment for the trial disease groups (i.e., non-small cell lung cancer, colon cancer, breast cancer, prostate cancer, kidney cancer, lymphoma) using generalized estimating equations, accounting for intra-disease random effects and trends across the 12 months (9 months exposure per trial). These results will then be put into context of the historic recruitment for these diseases at the center. We will also explore patient characteristics between the two groups to examine where differences might lie. Exploratory variables will also include the number of open trials and amendments to the trials and changes to status. Effect size estimate of the number of people to enroll cancer trials as a result of targeted social media listening and recruitment (SML) via Twitter. |

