### 3.3 Study design

#### 3.3.1 General study design

We will use a mixed-methods interrupted time series study design with a before and after intervention at the USC Norris Comprehensive Cancer Center (USC Norris). This study will examine the feasibility and gain preliminary data on the impact of targeted social media listening (SML) as a tool for enhancing recruitment to cancer trials (non-small cell lung cancer, colon cancer, breast cancer, prostate cancer, kidney cancer, lymphoma) among Twitter users in LA County. Disease categories will be randomized and rolled in consecutively, one every two weeks in the first quarter. The order will be randomized.

We aim to recruit all interventional trials in the select disease areas (84; based on USC Norris data from 1/1/2017 to 07/07/2017) open for recruitment to accrual for treatment of patients with non-small cell lung cancer, prostate cancer, breast cancer, colon cancer, kidney cancer, or lymphoma) at USC Norris. We may include another tumor type if the number of trials is insufficient or other tumor types and Twitter user activity emerge that are of interest to the research question. Disease categories will be randomized and rolled in consecutively, one every two weeks in the first quarter. Once a study is enrolled it stays on for the period of this study. Each trial will be exposed to the intervention for 9 months. This design was chosen to fit within the triage protocol of USC Norris and cause minimal disruption to the staff. Success will be compared to historical success achieved without the use of SML.

Outcomes will be the feasibility of the study described by the acceptance of and satisfaction with SM recruitment method among USC Norris study team members and Twitter users in LA County and by describing the proportion of eligible cancer trials to be enrolled in the study, cancer disease types and studies that can be monitored at a time, eligible participants that can be enrolled, diversity of participants, staffing required to monitor eligible studies, burden of recruitment/cost of intervention.

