**Figure 1. Study flow diagram of study design, procedures and stages for intervention A.**

## PARTICIPANTS

General characteristics of the proposed participant population(s): Any Twitter user who mentions one or more of the pre-selected cancer disease topics will be contacted via Twitter.

Anticipated number of research participants: We anticipate increasing the number of participants enrolled per trial and per month based on the following historic data from the past five years (see **Appendix 2**):

- Non-small cell lung cancer: Minimum of 2 participants per month
- Colon cancer: Minimum of 2 participants per month
- Prostate cancer: Minimum of 3 participants per month
- Breast cancer: Minimum of 2 participants per month
- Kidney cancer: Minimum of 1 participants per month
- Lymphoma: Minimum of 1 participants per month

Inclusion criteria for prospective trial participants: We will include all prospective trial participants in this study that come from Twitter in response of our SM recruitment interventions, provided they meet the specific trial's eligibility criteria.

Exclusion criteria for prospective trial participants: Persons who do not meet the eligibility criteria of any of the trials open to accrual will be excluded from participation, and persons who may be eligible (e.g., disease/histology, stage, prior treatment) but do not meet additional trial-specific requirements such as insurance or allergy to drug). These may vary by clinical trial. We will count these people as engaged but not enrolled and document the specific reasons.

Screening procedures: We will use the eligibility criteria as outlined above to verify clinical eligibility for participation in the study.

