## APPENDIX 2: ACCRUALS and ACCRUAL TARGETS BY TUMOR TYPE

Lung, Colon, Breast, Prostate, Kidney and Lymphoma

| Patient Accrual Diagnosis Site: Lung             |      |      |      |      |      |      |
|--------------------------------------------------|------|------|------|------|------|------|
| Trial Category                                   | 2017 | 2016 | 2015 | 2014 | 2013 | 2012 |
| Interventional Therapeutic                       | 17   | 33   | 34   | 19   | 16   | 32   |
| Interventional (Therapeutic and Non-Therapeutic) | 19   | 37   | 34   | 19   | 16   | 32   |

\*2017 accruals are from 1/1/2017 to 06/27/2017.

| Patient Accrual Diagnosis Site: Colon            |      |      |      |      |      |      |
|--------------------------------------------------|------|------|------|------|------|------|
| Trial Category                                   | 2017 | 2016 | 2015 | 2014 | 2013 | 2012 |
| Interventional Therapeutic                       | 21   | 49   | 83   | 81   | 45   | 47   |
| Interventional (Therapeutic and Non-Therapeutic) | 21   | 49   | 83   | 81   | 46   | 47   |

\*2017 accruals are from 1/1/2017 to 06/27/2017.

| Patient Accrual Diagnosis Site: Breast           |      |      |      |      |      |      |
|--------------------------------------------------|------|------|------|------|------|------|
| Trial Category                                   | 2017 | 2016 | 2015 | 2014 | 2013 | 2012 |
| Interventional Therapeutic                       | 33   | 64   | 63   | 79   | 104  | 151  |
| Interventional (Therapeutic and Non-Therapeutic) | 35   | 75   | 117  | 167  | 162  | 211  |

\*2017 accruals are from 1/1/2017 to 06/27/2017.

| Patient Accrual Diagnosis Site: Prostate         |      |      |      |      |      |      |
|--------------------------------------------------|------|------|------|------|------|------|
| Trial Category                                   | 2017 | 2016 | 2015 | 2014 | 2013 | 2012 |
| Interventional Therapeutic                       | 21   | 52   | 68   | 69   | 68   | 58   |
| Interventional (Therapeutic and Non-Therapeutic) | 23   | 52   | 68   | 71   | 68   | 79   |

\*2017 accruals are from 1/1/2017 to 06/27/2017.

| Patient Accrual Diagnosis Site: Kidney           |      |      |      |      |      |      |
|--------------------------------------------------|------|------|------|------|------|------|
| Trial Category                                   | 2017 | 2016 | 2015 | 2014 | 2013 | 2012 |

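### The study is labelled an interrupted time series with history as its only control, but the historic window is not fixed and the only trend named covers the 12 study months

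*Protocol*

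**What the plan says.** Section 3.3.1 names the design: "We will use a mixed-methods interrupted time series study design with a before and after intervention". The same section, the control-group entry of the synopsis and section 3.3.4 make historic recruitment at the centre the only comparator; section 3.3.4 states that there is no active control group.

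Section 3.3.7 describes the analysis in two places. For outcomes in general: "Comparisons of the before- and after time periods will be made using generalized estimating equations for appropriate outcome type", with patient and study characteristics explored "by including them as potential covariates in the models". For the efficacy aim, monthly actual recruitment is set against projected recruitment "and compared to historic data by trial disease group using generalized estimating equations", the model "accounting for intra-disease random effects and trends across the 12 months (9 months exposure per trial". The synopsis gives history a softer role, as context for the actual-versus-projected result, and adds: "Exploratory variables will also include the number of open trials and amendments to the trials and changes to status".

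None of these passages says which years are the historic period. A span is given only in section 3.3.3 under the participants heading, where anticipated numbers are "based on the following historic data from the past five years". The historic data supplied are the yearly counts in Appendix 2, in tables such as "Patient Accrual Diagnosis Site: Breast", each with a therapeutic row and a therapeutic-plus-non-therapeutic row.

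**The concern.** An interrupted time series gets its credibility from a pre-intervention series: the level and slope before the change predict what would have happened without it. A trend across the study year does not supply that. Disease groups roll in one every two weeks, so if the 12 months begin at the first roll-in, the first group has no unexposed time and the sixth has about 5 × 2 = 10 weeks. The counterfactual must then come from the historic series, whose window, eligibility filter and trend handling are left open.

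This matters because the series moved a good deal, and differently by cancer, before any outreach began. It is also not like for like. Appendix 2 counts by diagnosis site (all lung, where the study takes non-small cell only) and does not show this study's filters on phase, accrual target and remaining recruitment time. Section 3.3.7 sets p-values aside in favour of observed effect sizes, and Table 4 says the estimates will support a larger grant application. A before/after point estimate displaced by the choice of baseline would therefore be a defect in one of the pilot's main products.

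**Working it through.** **What the protocol itself states.** It gives no effect size or power for the impact comparison. Its only historic-rate figures are the monthly minima in section 3.3.3: lung 2, colon 2, prostate 3, breast 2, kidney 1, lymphoma 1. Read as disease totals, these do not match Appendix 2. The lowest year in 2012-2016 divided by 12 gives lung 16/12 = 1.33, colon 45/12 = 3.75, prostate 52/12 = 4.33, breast 63/12 = 5.25, kidney 7/12 = 0.58 and lymphoma 7/12 = 0.58. A per-trial reading cannot be checked. These figures therefore do not settle the baseline.

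**Inputs.** Therapeutic rows of Appendix 2; the 2017 column runs from 1 January to 27 June, which is 178 days.

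| Group | 2012 | 2013 | 2014 | 2015 | 2016 | 2017 (178 d) |
|---|---|---|---|---|---|---|
| Lung | 32 | 16 | 19 | 34 | 33 | 17 |
| Colon | 47 | 45 | 81 | 83 | 49 | 21 |
| Breast | 151 | 104 | 79 | 63 | 64 | 33 |
| Prostate | 58 | 68 | 69 | 68 | 52 | 21 |
| Kidney | 30 | 36 | 49 | 27 | 7 | 4 |
| Lymphoma | 12 | 11 | 8 | 7 | 9 | 4 |
| Total | 330 | 280 | 305 | 282 | 214 | 100 |

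Annualised 2017 total: 100 × 365/178 = 205.1.

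**Formula.** Rate ratio under no effect = (recent count / recent months) ÷ (2012-2016 count / 60). Recent months = 12 + 12 × 178/365 = 17.85.

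| Group | Recent count | Recent per month | 2012-2016 per month | Ratio |
|---|---|---|---|---|
| Lung | 50 | 2.80 | 134/60 = 2.23 | 1.25 |
| Colon | 70 | 3.92 | 305/60 = 5.08 | 0.77 |
| Breast | 97 | 5.43 | 461/60 = 7.68 | 0.71 |
| Prostate | 73 | 4.09 | 315/60 = 5.25 | 0.78 |
| Kidney | 11 | 0.62 | 149/60 = 2.48 | 0.25 |
| Lymphoma | 13 | 0.73 | 47/60 = 0.78 | 0.93 |
| Total | 314 | 17.59 | 1411/60 = 23.52 | 0.75 |

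On this reading the intervention would have to add 23.52 − 17.59 = 5.93 patients a month (5.93/17.59 = 34%) to look neutral.

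**Sensitivity of the total to the baseline.**
- Adding non-therapeutic trials: (229 + 106)/17.85 = 18.77 a month against 342.0/12 = 28.5, ratio 0.66.
- Window 2013 to mid-2017: 1181 patients over 4.488 years = 263.2 a year, against 17.59 × 12 = 211.1, ratio 0.80.
- 2016 alone as baseline, with annualised 2017 as the later rate: 205.1/214 = 0.96.

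The choice of window alone moves the answer from about 0.75 to about 0.96.

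**Would a fitted trend cure it?** A Poisson log-linear trend on the 2012-2016 totals falls 7.8% a year and predicts 219.4 for 2017, against 205.1 annualised (−6.5%). Group by group it does poorly: kidney 16.4 predicted against 8.2, colon 74.7 against 43.1, breast 42.6 against 67.7. A long baseline with group-specific slopes is therefore no remedy. An open-trial offset cannot be tried, because no historic open-trial counts are given.

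**The case against.** A reader might infer that the protocol plans to set nine months of outreach against a five-year mean, and that a null intervention will therefore look like a 25% loss. The documents do not support that. The five-year span is attached only to anticipated numbers, and no analysis passage fixes a window. The headline contrast is actual versus projected accrual; if targets fell as trials closed, that ratio need not fall with the counts. Despite its title, Appendix 2 as shown contains no historic targets, so the bias on that measure cannot be worked out in either direction.

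Nor did accrual fall steeply throughout. Totals for 2012-2015 were 330, 280, 305 and 282. Breast and kidney fell sharply, colon and prostate only in 2016-17, lymphoma changed little and lung rose, so some groups would show a false gain. The kidney ratio rests on 7 and 4 patients.

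It would also be wrong to say that every impact result is compromised. Messages are tagged, tracking sheets separate Twitter enrollees from other channels, and the enrolment rate in Table 3 divides by people contacted on Twitter. None of that uses the historic series.

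Finally, open-trial counts are not ignored, study characteristics are potential covariates, and segment terms and offsets are often left to a statistical analysis plan, which is not shown here. All of this stands and narrows the point. It does not remove it: section 3.3.7 itself names a trend term, that term covers the study year, and the text puts the historic comparison inside the model rather than beside it.

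**Conclusion.** The point holds in a conditional form. As written, the model does not deliver the interrupted time series that section 3.3.1 announces, and the undefined historic window leaves the size, and in some groups the direction, of the before/after estimate to a later choice. The ratios of 0.75 overall, 0.25 in kidney and 1.25 in lung rest on two assumptions: an unadjusted 2012-2016 therapeutic mean as comparator, and no-effect accrual that stays at its January 2016 to 27 June 2017 level. They illustrate how far the baseline can move the answer and do not predict the study's result. They apply to raw counts only. The analysis should be settled before study accrual data are seen.

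**What to change.** In section 3.3.7 and the synopsis, specify the before/after generalized estimating equations as a count model on monthly accrual by disease group:

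- a fixed, recent pre-period (for example the 18-24 months before roll-in) plus the study months;
- a pre-intervention time trend pooled across groups, with group-specific slopes only where counts allow;
- a level change at each group's own randomised roll-in date;
- an offset for log open eligible trial-months, or for projected accrual if the actual/projected ratio is kept;
- a pre-period restricted to therapeutic trials that meet the study's eligibility filter, with non-small cell only for lung.

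Keep the Appendix 2 multi-year figures as context, and give history the same role in the synopsis and in 3.3.7.

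The cost is a wording change and one registry extract of monthly accruals and open-trial counts, or of targets for the alternative offset. The documents do not show whether the registry can apply the eligibility filter retrospectively, so that needs checking. Intervals will be wider than with a long baseline. Kidney and lymphoma, with 11 and 13 therapeutic patients from January 2016 to 27 June 2017, will give imprecise group estimates and should be reported as such.
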